### Ivermectin may reduce the incidence of NS/OAE

In the NS-affected areas of South Sudan (Western Equatoria) and northern Uganda (Kitgum, Pader and Lamwo), CDTi coverage was respectively low or not implemented at all in the past because of civil conflict. However, in northern Uganda, bi-annual mass distribution of ivermectin and larviciding of rivers infested by blackflies was introduced in 2012, and subsequently no new cases of NS have been reported since 2013 [18]. In contrast, in South Sudan where insecurity as a result of civil conflict continued to prevent the implementation of CDTi, new cases of NS/OAE continue to emerge [12].

Less ivermectin use before the onset of epilepsy was reported in persons with epilepsy compared to age matched controls during the same period in Democratic Republic of the Congo [19, 20]. Since CDTi, because few new children develop OAE, an age shift of NS/epilepsy cases towards older ages (20 years or above) has been observed [21, 22]. Moreover there is anecdotal evidence that ivermectin may reduce the frequency and severity of seizures [23].

Therefore we will carry out a population-based intervention to investigate if a CDTi programme is indeed able to reduce the incidence of NS/OAE in onchocerciasis-endemic areas in South Sudan. We hypothesise that in the Mundri and Maridi Counties of South Sudan, the implementation of bi-annual CDTi with a 100% geographical coverage and a minimum of 80% coverage of ivermectin eligible individuals will reduce the incidence of NS/OAE by at least half (50%). This assumption is based on findings from Uganda where no new cases of NS appeared after bi-annual administration of ivermectin and larviciding of rivers. In South Sudan larviciding of rivers will not be done, so the effect of ivermectin alone may not be as efficient. Moreover, other forms of epilepsy not related to onchocerciasis will not be preventable by ivermectin treatment.

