#### Community-directed treatment with ivermectin (CDTi)

Following the initial household survey, CDTi will be implemented. The CDTi will be applied twice a year (6 months apart). The standard ivermectin dose of 150 μg/kg will be used [30]. Prior to implementation of the CDTi, the study team including community workers will meet with village and community leaders to explain the concept of CDTi. Community-directed distributers (CDDs) for the ivermectin will be trained to: (i) conduct a census; (ii) use measuring sticks to establish the number of ivermectin tablets to be given; (iii) detect and treat minor ivermectin side effects; (iv) refer cases of severe adverse events to the nearest health facility; (v) fill household treatment forms; (vi) keep an ivermectin inventory; and (vii) maintain CDTi distribution records and submit a report to the study coordinator. The Onchocerciasis Elimination Programme under the department of Preventive Chemotherapy, Neglected Tropical Diseases (PC-NTDs) in the Ministry of Health will coordinate the process. Ivermectin for the study will be supplied by the department of PC NTDs. Obtaining optimal CDTi coverage will be essential in order to be able to document an effect of the intervention. Therefore we plan to implement an epilepsy onchocerciasis awareness campaign in order to obtain > 90% CDTi coverage of eligible individuals. To reach this target we will get support from the state administration, and community involvement using the state radio, churches, mosques, community meetings and using the same research assistants to make house to house visits.

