### Sample size

We expect a crude incidence of new onset cases of NS/OAE in the Mundri/Maridi areas to be about 1.67% per year in all children aged five to 15 years [31]. With > 90% coverage of eligible individuals and 100% geographical coverage in the study area, we expect to decrease the incidence of NS/OAE in the five to 15-year-old population by 50%. Based on the reference proportion of 0.0150 (1.5% per year), alpha 5%, statistical power 80%, 2-sided testing, a total of 3475 children aged five to 15 years old need to be included in the study.

An adaptive study design will be used to ensure an adequately powered study. The NS/OAE incidence data will be cleaned after around 3000 children have been enrolled. The required sample size will be re-calculated using the actual observed incidence rate to ensure the study is adequately powered.

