### Data analysis

The unit of analysis will be children between the ages of 5 to 15 years, who are most vulnerable for the development of NS/OAE. The incidence rate of NS/OAE at baseline will be calculated using incident cases in children 5 to 15 years of age during the preceding 24 months. This rate will be compared with the incidence rate of NS/OAE in the 24-month interval between the first and the second household surveys.

Data will also be collected on recent deaths that might be attributed to recent onset NS and other forms of epilepsy (household heads and community informants will be questioned). Deaths suspected to be because of NS/OAE will be considered as incident cases.

Descriptive statistics will be employed to present retention rates. Means and standard deviations will be presented for continuous outcome measures and frequencies and percentages will be presented for categorical variables. Chi-squared tests will be used to compare any group differences for categorical variables and *t*-tests will be used for continuous variables.

The incidence of NS/OAE pre- and post-intervention will be compared among those who received ivermectin twice a year over 2 years and those who missed at least one dose of ivermectin.

Conflict induced displacement of people during the study period is possible. In case of in or out migration only the data will be analysed of families who stayed for at least 5 years in the area.

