### Limitation

A challenge for the study will be the insecurity in the region and the migration of people as a consequence. Ideally a clustered randomised controlled trial would be preferred in which one population receives ivermectin treatment and the other not. However, given the expected benefits of CDTi, withholding treatment is ethically not acceptable. Indeed in onchocerciasis-endemic regions all eligible individuals should receive ivermectin at least annually [32]. Comparing annual with bi-annual ivermectin treatment would be a possibility but this would require a very large sample size because of the relatively low incidence of epilepsy. Moreover, to achieve the elimination goal for onchocerciasis and based on success stories from the Americas and other African countries, a bi-annual CDTi strategy is preferred, especially where the onchocerciasis situation is insufficiently controlled [33–35]. Given the dramatic decrease of incidence of NS/OAE as a consequence of bi-annual CDTi and larviciding of rivers in northern Uganda [36], we expect that with an optimal bi-annual CDTi programme with > 90 coverage of eligible individuals, we will be able to show a similar decrease of incidence of NS/OAE in South Sudan.

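### The adherence comparison pools children with zero to three rounds of ivermectin; if the effect is graded, the contrast is diluted and weakly powered, so a null would not be evidence against CDTi

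*Protocol article*

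**What the plan says.** The main analysis is before/after. NS/OAE incidence in children aged 5 to 15 over the 24 months before baseline is calculated, and "This rate will be compared with the incidence rate of NS/OAE in the 24-month interval between the first and the second household surveys". The hypothesised 50% reduction is sized in the Sample size section for that comparison.

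A later sentence of Data analysis adds an adherence comparison. It opens "The incidence of NS/OAE pre- and post-intervention will be compared among those who received ivermectin twice a year". In full, incidence is to be "compared among those who received ivermectin twice a year over 2 years and those who missed at least one dose of ivermectin", which sets fully treated children against everyone who missed one dose or more.

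Rounds are six months apart (section on CDTi) and the second survey comes two years after the first (Study procedures). Four rounds are implied, though the number is not stated. The hypothesis assumes at least 80% coverage of eligible people. The CDTi section plans an awareness campaign "in order to obtain > 90% CDTi coverage of eligible individuals", and the Sample size section uses the same figure. Distributors are to fill in household treatment forms and keep distribution records.

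The protocol does not say how rounds received are distributed per child, how far missing one round predicts missing another, or what dose-response is expected.

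**The concern.** There is no untreated arm, so a fall between the two periods could also reflect secular change, displacement or differences in recall. The adherence comparison is the natural check on those explanations, because it alone contrasts levels of exposure within one period.

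Its lower group is defined only by not being complete. A child with three of four rounds is counted with a child who had none. If coverage is high and each round adds some protection, most of that group carries much of the benefit, and the contrast with fully treated children shrinks. The Limitation section says of a related contrast: "Comparing annual with bi-annual ivermectin treatment would be a possibility but this would require a very large sample size".

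At stake is how the result is read. The Discussion section expects the findings to influence communities, policy makers and funders. A non-significant contrast without a caveat could be taken to mean that ivermectin does not prevent NS/OAE, or that missed rounds do not matter.

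**Working it through.** **Plan's own figure.** The protocol gives 3475 children for 1.5% per year, a 50% reduction, two-sided 5% and 80% power. Two proportions, 0.015 v 0.0075, give 3104 per period, or 3365 with continuity correction. Reading the 50% as an odds ratio of 0.5, with continuity correction, gives 3422. The figure is thus a near miss on the literal inputs and close to a per-period number. Nothing below depends on it beyond its use as the number of children.

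**Inputs from the protocol.** Coverage c = 0.90 or 0.80; N = 3475; 50% reduction; four rounds (2 per year × 2 years).

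**Assumptions not in the protocol.** Untreated 24-month risk 2 × 1.5% = 3%; the 50% reduction is reached at four rounds; rounds follow Binomial(4, c), or a beta-binomial with within-child correlation ρ; all N are followed up.

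**Step 1, make-up of the missed group (c = 0.90, independent rounds).** All four: 0.9⁴ = 65.6%. Missed at least one: 34.4%. Within the latter, P(k)/0.3439 gives 84.8% with three rounds, 14.1% with two, 1.1% with one and 0.03% with none.

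**Step 2, expected ratio.** Risk relative to untreated after k rounds is 1 − 0.5k/4 (linear) or 0.5^(k/4) (log-linear).
- Linear, missed group: 0.848 × 0.625 + 0.141 × 0.75 + 0.011 × 0.875 + 0.0003 × 1 ≈ 0.645. Ratio 0.5/0.645 = 0.78.
- Log-linear, missed group: 0.613. Ratio 0.5/0.613 = 0.82.

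**Step 3, power (linear case).** Missed: 3475 × 0.3439 = 1195 children at 0.03 × 0.645 = 1.94%. Complete: 2280 children at 1.50%. The difference is 0.0044. The standard error is 0.0045 under the null (pooled) and 0.0047 under the alternative. Φ[(0.00436 − 1.96 × 0.00455)/0.00473] = Φ(−0.96) ≈ 0.17.

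**Step 4, other settings.**

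| Coverage, ρ | Three rounds, % of missed | Two or three, % of missed | Linear: ratio, power | Log-linear: ratio, power |
|---|---|---|---|---|
| 90%, 0 | 84.8 | 98.9 | 0.78, 17% | 0.82, 13% |
| 80%, 0 | 69.4 | 95.4 | 0.75, 19% | 0.79, 14% |
| 90%, 0.2 | 65 | 90 | 0.73, 22% | 0.77, 17% |
| 90%, 0.5 | 43 | 67 | 0.66, 31% | 0.69, 27% |
| 80%, 0.5 | 37 | 61 | 0.64, 43% | 0.67, 37% |

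**Step 5, other dose-response shapes (90%, independent).** If only all four rounds protect, the ratio is 0.50 with 82% power. If any single round gives full benefit, it is 1.00.

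**Step 6, other reading of the sentence.** If it means before/after within each adherence group (linear, 90%, independent), power is about 93% among complete children and 39% in the missed group, whose expected ratio to the earlier period is 0.65.

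**The case against.** A reader might infer that this contrast cannot show the 50% effect, that it would look null even if CDTi works, and that its comparator is mostly children with three of four rounds. The documents do not support any of these as stated.

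- **The 50% effect is not assigned to this sentence.** It is tested by the before/after comparison. This stands: the flaw is in a supporting analysis.
- **The sentence can be read as before/after within each group.** On that reading the complete group would be expected to show a clear fall. This also stands. The lower group remains a mixture of zero to three rounds, and comparing the two groups brings the dilution back.
- **The three-round share depends on unstated adherence patterns.** It falls to 43% (90% coverage) or 37% (80%) at correlation 0.5, and to none if all non-coverage is persistent. What holds is that the group is mostly partly treated when rounds are independent or moderately correlated.
- **The ratio depends on an unstated dose-response.** It runs from 0.50 to 1.00, so neither a null nor a clear effect can be predicted.
- **Bias may run the other way.** Very ill patients are ineligible, and suspected NS/OAE deaths count as cases. An early case can therefore fall into the missed group because of the illness, which inflates the apparent benefit. This does not offset the dilution in any known amount and makes the result harder to read.
- **The Limitation remark on sample size concerns an alternative trial design.** It is an analogy and not an admission about this analysis.
- **Modelling detail may sit in an unseen analysis plan.** That is fair for the choice of model. The split itself is fixed in the protocol.

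**Conclusion.** The point holds in limited form. The protocol fixes a two-group split whose lower group mixes zero to three of about four rounds. If the effect is graded, the contrast is diluted to a ratio of about 0.64 to 0.82 and has about 13% to 43% power. These figures rest on four rounds, 80% to 90% coverage, within-child correlation from 0 to 0.5, 3475 children and a 3% untreated 24-month risk.

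The contrast does not estimate the effect of CDTi. A non-significant result would not be evidence against the programme, and a significant one could partly reflect illness that caused missed rounds. The primary before/after test is unaffected.

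**What to change.** In Data analysis:

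1. State whether the adherence sentence means a comparison between groups after the intervention, or before/after within each group.
2. Keep the split if wanted, but label it complete versus incomplete adherence and say that it does not estimate the CDTi effect.
3. Add, from the household treatment forms, a table of NS/OAE incidence by number of rounds received (0 to 4) and a rate ratio per additional round with a confidence interval from a log-link model.
4. Count only rounds received before onset, and assign person-time to each level as rounds accrue, so that illness or death does not itself place a case in the low-exposure group.
5. Do not use zero or one round as the sole reference group. At 90% coverage with independent rounds it would hold about 13 children (3475 × 0.0037).

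The cost is analysis wording and linkage of round-level records that distributors already keep. The gain in power is modest. Under a linear effect a per-round trend moves power from 17% to 18% (90% coverage, independent rounds), from 19% to 26% (80%, independent) and from 43% to 54% (80%, correlation 0.5). If only complete treatment protects, the trend does worse than the split: 82% falls to 77% at 90% coverage, and 83% to 65% at 80%. That is a reason to add the trend and not to substitute it. The per-round ratio assumes a dose-response shape, which the table by rounds lets readers check.

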##### Definitions

A *case of epilepsy* will be defined based on the International League Against Epilepsy (ILAE) as an individual with at least two unprovoked seizures with a minimum of 24 h separating the two episodes [27].

*Active epilepsy* will be defined as a person who is taking anti-epileptic treatment or who is not on anti-epileptic treatment but had at least one episode of seizures during the last 5 years.

A *new case of epilepsy* will be defined as a person who developed the first seizures within the last 24 months preceding the baseline survey (pre-CDTi incidence), or a person who developed the first seizures after the first round of CDTi and the second study visit to the household (post-CDTi incidence).

A *suspected NS case* will be defined as a person who presented with episodes of reduced consciousness with the head dropping forward repeatedly.

*OAE* will be defined as a person meeting the following six criteria: 1) Three years of living in an onchocerciasis-endemic region; 2) High prevalence of epilepsy in the village and families with more than one child with epilepsy; 3) History of at least two unprovoked epileptic seizures at least 24 h apart; 4) No obvious cause for the epilepsy; 5) Onset of epilepsy between the ages of three and 18 years; 6) Normal psychomotor development before the onset of epilepsy.

Epilepsy caused by perinatal trauma, head trauma, meningitis/encephalitis, and cerebral malaria can be suspected through medical history taking. Epilepsy caused by cysticercosis is difficult to differentiate from OAE but in the Maridi and Mundri areas there are no pigs, therefore neurocysticercosis does not exist in these areas. It is expected that the prevalence of epilepsy not caused by onchocerciasis will be < 1.4% (the median prevalence of epilepsy in Sub-Saharan Africa) [28].

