### Exclusion criteria for ivermectin treatment

Children < five years old, pregnant women, women who have been lactating less than seven days, or very ill patients are ineligible.

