### Study procedures

Pre- and post-intervention household surveys will be performed using exactly the same methodology. The pre-intervention survey will be done within two months before the start of the bi-annual CDTi. A post-intervention survey will be done 2 years later.

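### The comparison of children who took every ivermectin round with those who missed one counts doses due after seizure onset, so it can show a spurious effect, protective if cases miss later rounds

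*Protocol article*

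**What the plan says.** After the main before/after analysis, the Data analysis section adds a comparison by ivermectin intake. It has the rates from before and after the intervention "compared among those who received ivermectin twice a year over 2 years and those who missed at least one dose of ivermectin". Five other statements bear on how that split works:

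- **Outcome window.** Post-intervention incidence is the "incidence rate of NS/OAE in the 24-month interval between the first and the second household surveys" (Data analysis).
- **Case definition.** A post-CDTi case is one whose first seizure falls between the first round and the second household visit (Definitions).
- **Schedule.** Rounds are six months apart (CDTi section), and "The pre-intervention survey will be done within two months before the start of the bi-annual CDTi" (Study procedures). Four rounds therefore fall at about months 0–2, 6–8, 12–14 and 18–20 after the baseline survey.
- **Deaths.** "Deaths suspected to be because of NS/OAE will be considered as incident cases" (Data analysis).
- **Eligibility.** "Children < five years old, pregnant women, women who have been lactating less than seven days, or very ill patients are ineligible" (Exclusion criteria for ivermectin treatment). Epilepsy itself is not an exclusion.

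Nothing in the article limits the doses that define the two groups to those taken before the first seizure.

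**The concern.** Exposure and outcome share one 24-month window, and exposure is fixed only at its end. A child whose seizures begin at month 8 is classified partly by rounds at about months 12 and 18, which cannot have prevented that onset. If the illness affects whether those rounds are taken, the outcome determines the exposure group.

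The protocol supplies two such routes. A child who dies of suspected NS/OAE before the last round counts as a case and cannot have taken every round. A child who becomes very ill is ineligible for later rounds. Age is a third, separate problem. Children under five at an early round may be counted as having missed it, depending on how missed is read and at which survey age is taken. They differ in age from the completers, and the direction of that effect is unknown.

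The study has no control group, and this is the only comparison by ivermectin intake that the article states. A spurious protective ratio could be read as support for a causal effect.

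**Working it through.** The protocol gives no figure for this comparison, so there is nothing to reproduce. The check asks what the comparison would show if ivermectin had no effect.

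**Inputs from the protocol.** Incidence is 1.5% per year, so about 3% over 24 months. There are four rounds six months apart, the first 0–2 months after the survey. Coverage is planned above 90% of eligible people. The sample size is 3475 children.

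**Assumptions, not in the protocol.**
- Onset is even over time.
- The share c who would complete all rounds, apart from any effect of onset, runs from 0.9^4 = 0.656 (rounds independent) to 0.90 (the same children each time).
- Q is the share of cases who miss their remaining rounds because of onset.
- All 3475 children are followed after the intervention.

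**Step 1: share of onsets before the last round, f.** With no lag, f = 18/24 = 0.75. With a two-month lag, f = 20/24 = 0.83. The central value, with rounds at months 1, 7, 13 and 19, is f = 19/24 = 0.79.

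**Step 2: null risks.** Because cases are rare, the group sizes are treated as fixed:

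- risk in completers = 0.03 × (1 − Qf)
- risk in missed = 0.03 × [1 − c(1 − Qf)] / (1 − c)

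For Q = 10%, 1 − Qf = 1 − 0.1 × 0.7917 = 0.9208, and the completers' risk is 2.76%.

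- c = 0.656: missed = 0.03 × (1 − 0.604)/0.344 = 3.45%. Ratio 0.80.
- c = 0.90: missed = 0.03 × (1 − 0.829)/0.10 = 5.14%. Ratio 0.54.

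| Q | Null ratio, c = 0.656 | Null ratio, c = 0.90 |
|---|---|---|
| 0 | 1.00 | 1.00 |
| 5% | 0.89 | 0.71 |
| 10% | 0.80 | 0.54 |
| 20% | 0.65 | 0.35 |
| 30% | 0.53 | 0.24 |

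A simulation of 4 million children gave 0.82 and 0.54 at Q = 10%, and 0.54 and 0.26 at Q = 30%.

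**Step 3: why high coverage makes it fragile.** Of 3475 children, about 3475 × 0.03 = 104 become cases. With c = 0.90, 93.8 would be among completers and 10.4 among the missed. At Q = 10%, 93.8 × 0.0792 = 7.4 cases change group, giving 86.4 and 17.9. Seven misplaced cases raise the risk in the missed group from 3.0% to 5.1%.

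**Step 4: chance of a false protective result.** With a two-sided 5% test of two proportions, the chance of a significant result favouring completers is 2.5% at Q = 0. It is 21% (c = 0.656) to 65% (c = 0.90) at Q = 10%, and 91% or more at Q = 30%.

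**Step 5: opposite direction.** If onset makes a case with rounds remaining 20% more likely to complete (Q = −0.2, c = 0.656), the ratio is 1.61 at f = 0.75 and 1.71 at f = 0.83, a false harm.

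**Step 6: the other reading of the sentence.** Suppose it means post versus pre within each group, and baseline cases miss rounds at the same Q. At Q = 30%, the null post/pre ratio in completers is (1 − 0.3 × 0.7917)/(1 − 0.3) = 0.7625/0.70 = 1.09. In the missed group (c = 0.656) it is (1 − 0.656 × 0.7625)/(1 − 0.656 × 0.70) = 0.500/0.541 = 0.92. The bias is small and reversed.

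**Step 7: after correction.** With person-time classified by rounds taken before onset, the simulated null rate ratio was 0.99–1.01 for every Q from 0 to 1 under both coverage assumptions.

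**The case against.** The strongest objection is that all of the bias comes from Q, which the protocol does not give. With Q = 0 the ratio is exactly 1.00. A reader might infer that the comparison will show a large protective effect whatever ivermectin does, but the text does not support that. Epilepsy is not an exclusion, so a case who is not very ill can take every round. Several features could raise uptake among cases: the reported belief that ivermectin lessens seizures, the awareness campaign with house-to-house visits, and surveillance that brings new cases into care. This stands: neither size nor direction is settled. Even so, deaths before the last round and very ill cases act only towards the missed group, and a small Q is enough to matter.

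The sentence can also be read as pre/post within each group, where the bias is small and reversed. This stands too, and is a reason to state which contrast is meant.

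A reader might further infer that the study's main result is compromised, or that this split will carry the causal argument. The hypothesis, sample size and first-stated analysis all concern incidence before versus after CDTi in all children aged 5–15, which does not use dose completion. The split is one additional sentence.

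Lastly, a condensed article may leave modelling detail to a fuller plan. That covers the form of adjustment. It does not cover the rule defining the groups, which the article itself states.

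**Conclusion.** The point holds in a limited form. As stated, the split classifies children partly by doses due after onset or death, so it can show an effect where there is none. If 10% of cases miss their remaining rounds because of onset, the null ratio is about 0.54–0.80. That range rests on even onset, an assumed 66–90% of children completing, and an assumed Q. There is no bias at Q = 0, and it reverses if cases take more ivermectin. The comparison cannot be read causally as written, but the primary pre/post result is untouched. It is worth correcting before the analysis, and ranks below anything that must be fixed for the study as a whole.

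**What to change.** 1. State whether the sentence means completers versus missed in the post-CDTi period, or post versus pre within each group.
2. For the post-CDTi period, split each child's person-time at each distribution date and classify it by rounds received so far. Assign each case to the status held just before the first seizure, and end follow-up at onset or death.
3. Count only rounds for which the child was eligible, and adjust for age.
4. Label the comparison supportive. Families who take every round may differ from those who do not, and time-updating does not remove that.
5. Report why rounds were missed. Where onset cannot be placed before or after a round, give a sensitivity analysis under both placements.

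The cost is a little more programming and reliance on dated doses for each child and on recalled onset dates. The planned split already needs each child's dose history, and the definition of a new case already needs an onset date. The article mentions household treatment forms and distribution records but does not say that they hold dated doses by child, so this should be confirmed before the first round.

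### The dose comparison has no eligibility condition, so if age is taken at the second survey the missed-dose group collects children too young for the first round

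*Protocol article*

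**What the plan says.** The protocol article, Data analysis, plans a comparison of NS/OAE incidence before and after the intervention among "those who received ivermectin twice a year over 2 years and those who missed at least one dose of ivermectin". No condition on eligibility is attached. The only group tests named in that section are chi-squared and t-tests, and neither adjusts for age.

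The section on exclusion criteria for ivermectin treatment reads as follows: "Children < five years old, pregnant women, women who have been lactating less than seven days, or very ill patients are ineligible".

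On age, Data analysis says: "The unit of analysis will be children between the ages of 5 to 15 years". The baseline rate uses "incident cases in children 5 to 15 years of age during the preceding 24 months". The date at which age is taken (baseline, second survey or onset) is not given. Study procedures adds: "Pre- and post-intervention household surveys will be performed using exactly the same methodology".

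On timing, treatment rounds are six months apart (section on CDTi), the second survey follows the baseline survey by two years (abstract, Methods), and "The pre-intervention survey will be done within two months before the start of the bi-annual CDTi".

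**The concern.** The stated split has two groups and no place for a child who was not allowed ivermectin at a round. Such a child cannot have received every dose. Read literally, the only group left is the one that missed at least one.

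For pregnancy or severe illness this may touch few children aged 5 to 15, and the documents give no figure. For the under-five bar it depends on when age is taken. If a child counts as 5 to 15 at the second survey, the youngest two years of the band are almost entirely children who were 3 or 4 at the first round. Dose group and age are then tied together by the treatment rule, whatever families choose.

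The Background section describes onset as mainly between 5 and 15 years, and the OAE definition admits onset from age three. If risk differs between the youngest children and the rest, the two groups would differ in incidence with no effect of ivermectin at all. The study has no control population (Limitation), so this is its only internal comparison of more-treated with less-treated children.

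**Working it through.** The plan gives no figure for the dose comparison, so there is nothing to reproduce. Its sample size of 3475 belongs to the main before/after comparison and is not used here.

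**Inputs from the document.** Ivermectin barred below age 5; band 5 to 15 years; rounds six months apart; first round 0 to 2 months after the baseline survey; second survey 24 months after baseline; coverage of eligible people at least 80% (hypothesis) or above 90% (CDTi and Sample size sections).

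**Assumptions.** Four rounds in two years (inferred from the spacing); equal numbers at each age; band width of 10 years (5 to under 15) or 11 years (5 to under 16); age taken at the second survey.

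**Step 1: who is barred by age from the first round.** The first round falls 24 − 0 = 24 to 24 − 2 = 22 months before the second survey, so children up to 1.83–2.0 years above age five at that survey were under five at round one. The share s runs from 1.83/11 = 16.7% to 2.0/10 = 20%.

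**Step 2: their share of the missed-dose group.** With f the proportion of always-eligible children who take all four doses, the missed-dose group is s + (1 − s)(1 − f), and the barred children make up w = s divided by that sum.

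| Uptake per round | f | s | Missed-dose group | w |
|---|---|---|---|---|
| 90%, independent | 0.9^4 = 0.656 | 20% | 0.200 + 0.800 × 0.344 = 0.475 | 42% |
| 90%, independent | 0.656 | 16.7% | 0.167 + 0.833 × 0.344 = 0.453 | 37% |
| 80%, independent | 0.8^4 = 0.410 | 20% | 0.200 + 0.800 × 0.590 = 0.672 | 30% |
| 80%, independent | 0.410 | 16.7% | 0.167 + 0.833 × 0.590 = 0.659 | 25% |
| 90%, same children always missed | 0.9 | 20% | 0.200 + 0.800 × 0.100 = 0.280 | 71% |
| 90%, same children always missed | 0.9 | 16.7% | 0.167 + 0.833 × 0.100 = 0.250 | 67% |
| 80%, same children always missed | 0.8 | 20% | 0.200 + 0.800 × 0.200 = 0.360 | 56% |
| 80%, same children always missed | 0.8 | 16.7% | 0.167 + 0.833 × 0.200 = 0.333 | 50% |

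**Step 3: age difference.** With no lag and a 10-year band, the full-dose group has mean age (7 + 15)/2 = 11.0 and the barred children (5 + 7)/2 = 6.0. At 90% independent uptake the missed-dose group averages 0.421 × 6.0 + 0.579 × 11.0 = 8.9 years. Over all rows and both lags the means are about 11 to 11.5 years (full) against 7.4 to 10.0 years (missed).

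**Step 4: what this could do with no dose effect (illustration).** Take an 11-year band, no lag and 90% uptake, and let risk below age five be k times the risk from five on. Barred children spend on average one of the two follow-up years below five, so their mean relative risk is (1 + k)/2. The full/missed incidence ratio is 1 / [1 − w(1 − k)/2]. Here s = 2/11 = 18.2%, so w = 0.393 (independent uptake) or 0.690 (same children missed).

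- k = 0: 1/(1 − 0.393 × 0.5) = 1.24; 1/(1 − 0.690 × 0.5) = 1.53.
- k = 0.5: 1/(1 − 0.393 × 0.25) = 1.11; 1/(1 − 0.690 × 0.25) = 1.21.
- k = 1: 1.00 in both cases.
- k = 2: 1/(1 + 0.393 × 0.5) = 0.84; the direction reverses.

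The documents give no value for k.

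**Step 5: the other readings of age.** If the band is fixed at baseline, every child is at least five at round one and s = 0%. If follow-up time is counted while a child is aged 5 to 15, children who turn five after round one supply on average one year of age out of 11, about 9% of the time at risk.

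**The case against.** The strongest reply is that the text fixes neither element the concern needs. It does not say that a round at which a child was ineligible counts as missed. Coverage is expressed throughout for eligible people, so a missed dose can be read as one not taken when it could have been. Nor does the text say when age is taken. Because the dose comparison speaks of incidence both before and after the intervention, it can be read as following children who were 5 to 15 at baseline, and none of those was too young at round one. This is also a journal article, and the handling of exposure groups in a secondary comparison is often settled in the analysis plan.

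Much of this stands. A reader might infer that the protocol counts under-fives as having missed a dose; it does not say so. A reader might also infer that every child aged 5 or 6 at the second survey is affected. The lag of up to two months makes that too absolute, since a child aged 6 years 11 months then could have reached five by round one.

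It does not remove the point. The two-way split is stated in the protocol itself, without the eligibility qualifier used for coverage. The same-methodology statement in Study procedures favours age at each survey. Followed literally under that reading, the rule confounds dose group with age.

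**Conclusion.** The point holds conditionally. If age 5 to 15 is taken at the second survey and the split is applied as written, about 17–20% of the analysed children cannot be in the full-dose group. They form about 25–42% of the missed-dose group at 80–90% independent uptake, and 50–71% if the same children are missed each time. These figures assume uniform ages and four rounds. If age is fixed at baseline, the age problem is nil, though the pregnancy and illness exclusions remain unplaced.

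Two stronger conclusions are tempting, and the documents support neither. The first is that the comparison cannot show a dose effect: age is recorded, and restriction or age grouping removes this imbalance, so the groups may differ by age but the comparison is not beyond repair. The second is that the bias hides a benefit of ivermectin. That follows only if risk is lower below five. Onset mainly at 5 to 15 makes this plausible, but no incidence by age is given, so size and direction are unknown.

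The main before/after comparison does not use dose groups and is untouched by this point.

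**What to change.** In Data analysis:

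1. State the date at which age 5 to 15 is taken. Fixing it at baseline should not be the only remedy: children aged 5 to 15 at baseline cover ages from 5 − 2 = 3 looking back and up to 15 + 2 = 17 looking forward, so the choice also bears on the main comparison.
2. Restrict the dose comparison to children eligible for ivermectin at every round under the protocol's own exclusion criteria. Alternatively, count a dose as missed only at rounds where the child was eligible; this keeps more children but lets a child with fewer rounds count as complete.
3. Report children ineligible at any round as a separate group.
4. Compare dose groups within age groups.

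This takes a few sentences and should need no new data: age is needed for the analysis band anyway, and household treatment forms and distribution records are already planned. The cost is that the youngest children leave this secondary comparison, which remains non-randomised. No change to the ivermectin eligibility rule is proposed.
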